### Study design and randomization

The study will combine both qualitative and quantitative methods to achieve the study objectives. A formative study using participatory action research design will first be conducted. Then, a cluster randomized trial utilizing both qualitative and quantitative data collection methods will be conducted. The purpose of the formative qualitative study will be mainly to understand the local contexts and cultural factors that influence maternal nutrition, breastfeeding and other infant and young child feeding practices. This information will inform the adaptation of the intervention to the local contexts, and aid understanding of the potential barriers and facilitating factors to the implementation of the intervention. Another purpose of the formative study is to inform the finalization of quantitative data collection tools. Qualitative methods will be used at the formative stage as well as during and after the intervention to determine experiences with the intervention. Quantitative methods will mainly serve to determine effectiveness of the intervention with regards to breastfeeding practices and nutritional status.

The study will adopt a cluster-randomized trial design [18, 19]. For pragmatic purposes, community units (CUs), as defined by the government’s Community Health Strategy [20] will be used as the clusters. Thirteen CUs have been defined in the study areas. Twelve of the CUs will be randomized with half allocated to the intervention and the other half to the control arm without matching. The random sequence of allocation of the CUs to the intervention or control arm will be computer-generated. Cluster randomization is preferred over individual-level randomization to minimize contamination and for pragmatic purposes in case of future scale-up of the intervention. Randomization will be done by a data analyst who is not a primary member of the study team. Fig. 1 shows the study design schematically.

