### Clusters and study populations

Twelve CUs will constitute the clusters to be included in the study. CUs are geographically defined units, mostly equal to a village (in our study setting) and usually have a population size of approximately 5000 people. The CUs are defined by the Community health Strategy, a government community-based approach where community health workers (CHWs), currently referred to as community health volunteers (CHVs) in Kenya, provide health care services to people at the community level. The reason for choosing to work with the defined CUs is pragmatic because they are administrative areas that are defined by the health care system and any intervention moving forward in the future would need to map onto these administrative units to be effective [20].

This trial will include women of reproductive age (15–49 years) who are pregnant at the time of recruitment, and their respective children from the pregnancies aged less than 6 months in Koibatek sub-county in Baringo county. These will be recruited during pregnancy on a rolling basis until the desired sample size is achieved. The target is to recruit the women as early as possible during pregnancy, particularly during the first or second trimester, so as to get as much exposure to the intervention during pregnancy as possible.

Women of reproductive age, who will have given birth before receiving at least one personalized counseling session by our trained CHWs regarding exclusive breastfeeding will be excluded. To be dropped from the analysis will be: (i) women who lose their pregnancy and/or have a still-birth; (ii) women who cannot be traced for follow-up during pregnancy; (iii) mother-child pairs of children with disability that would make their participation in the intervention difficult: for example, blind, deaf and intellectually impaired individuals or children with cleft lip.

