The intervention group will also receive the BFCI package including: (i) personalized home-based counseling and support on optimal MIYCN practices by CHWs, and professional counseling of mothers by health professionals at health facilities; and (ii) formation of community support groups for mothers. In addition, they will receive MIYCN education materials. The control group will have the usual care only (Table 1). Usual care will include routine services offered to mothers and their children through the health care system including information materials regarding MIYCN, standard counseling on antenatal and postnatal care, appropriate tests during pregnancy, health facility delivery, general nutrition, hygiene, and immunization. Those in the control arm will receive routine visits by CHWs as provided for within the Community Health Strategy (usual care). Table 2 outlines the intervention package.

**Table 2 Tab2:** Services and materials provided to intervention and control groups

Intervention group	Control group
a) Distribution of MIYCN educational materials (usual care)	a) Distribution of MIYCN educational materials (usual care)
b) Supportive supervision (scheduled regular visits to assess implementation of BFCI package)	b) Supportive supervision (usual planned visits by DHMT)
c) CHW motivation package (provision of a monthly stipend (seed money for an income generating activity as a group) and training for income-generation activities as incentive)	c) CHW motivation package (Seed money for an income generating activity as a group same as in the intervention group)
d) Orientation, and continuous on job training and mentoring of the HWs and CHWs/CHEWs on BFCI package implementation	
e) Formation and support of mother support groups in the community	

*BFCI* Baby Friendly Community Initiative, *CHEWs* community health extension workers, *CHWs* community health workers, *DHMT* district health management team, *HWs* health workers, *MIYCN* maternal, infant and young child nutrition

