Counseling of mothers will be initiated during pregnancy as soon as the mother is recruited and will be continued until the infant is 6 months. Counseling will encompass maternal nutrition, skin-to-skin contact between mother and baby immediately after birth, immediate initiation of breastfeeding after birth, breast positioning and attachment, exclusive breastfeeding, frequency and duration of breastfeeding, expressing breast milk, storage and handling of expressed milk and lactation management. It will also focus on age-appropriate complementary feeding, starting at 6 months: age appropriate complementary foods (nutritious, safe, affordable, and locally available), feeding frequency and quantity, and appropriate feeding practices including hygiene and responsive feeding behaviors, which encourage mother-child interaction during feeding [24, 25]. However, effectiveness of the intervention on complementary feeding will not be evaluated in this study. For the intervention arm, CHWs will visit the pregnant woman about once every month up to week 34, after which they will visit the mother weekly until delivery. After delivery, they will visit the mother weekly in the first month, then once a month until 6 months. The CHWs to be involved will be existing CHWs within the existing CUs in the region under the Community Strategy. In line with guidelines of the Community Health Strategy in Kenya, each CHW will serve approximately 20 households. HIV-infected women will not be excluded nor their status identified in the data collection. The counselors in the intervention arm will be trained on the messages for both HIV-negative and HIV-positive mother with regards to infant feeding. The information materials given to both intervention and control arms will also stipulate information on feeding for HIV-exposed infants. The CHWs will further be told to inform the mothers that should they be HIV-positive, they should seek further counseling and support from health professionals/PMTCT program. An outline of the content of the counseling messages is given in Table 3.

**Table 3 Tab3:** Content of counseling messages

• Maternal nutrition:	
	Food portions during pregnancy and lactation
	Appropriate foods (nutritious, affordable, and locally available) during pregnancy and lactation
	Frequency of feeding during pregnancy and lactation
• Breastfeeding:	
	Breast positioning and attachment
	Immediate initiation of breastfeeding after birth
	Exclusive breastfeeding for 6 months

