The timing of the counseling/support has been found to be important. Prenatal and postnatal breastfeeding counseling interventions, whether alone or in combination have been found effective in improving breastfeeding practices including duration of exclusive breastfeeding and any breastfeeding [36, 37]. In a systematic review of effectiveness of breastfeeding interventions that involved 38 trials [36], prenatal breastfeeding interventions significantly increased the rate of any short-term breastfeeding (1–3 months) rate by 39 % compared to the usual care while combined prenatal and postnatal interventions significantly increased both the rates of intermediate (4–5 months) and long-term (6–8 months) any breastfeeding compared to usual care by 15 % and 33 % respectively. Postnatal interventions significantly increased the rates of short-term exclusive breastfeeding (1–3 months) by 21 %. In another systematic review that involved 20 trials, only interventions with a post-natal component were found to be effective in improving breastfeeding practices while there was no evidence to suggest effectiveness of antenatal counseling/support [37]. This study, which involves home-based and facility-based counseling/support during pregnancy and 6 months following delivery, will provide further evidence on the effectiveness of combined antenatal and postnatal counseling/support on breastfeeding and other infant feeding practices.

Some limitations to this study may include bias in reporting (mothers’ self-report) of the primary outcome (exclusive breastfeeding). To counter this, data will be collected longitudinally at various time points, and a thorough questioning using 24-hour recall on what the baby was fed on will be done to ensure that as true as possible a record of infant feeding practices is obtained. It is possible that even with randomization of clusters; there will be differences in the baseline measures in the intervention and control groups by chance. Analysis methods to be adopted will control for baseline differences, if such differences are identified, but this will reduce the statistical power. Though we do not expect much loss to follow-up as we will work with a stable rural agrarian community, we plan to adopt intention-to-treat analysis to deal with potential loss to follow-up. Additionally, we have included an allowance for loss to follow-up in the sample size determination.

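### Enrolled pairs can be dropped from the analysis after allocation on an open-ended judgement about taking part in the intervention, which could fall unequally on the two arms

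*Protocol article*

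**What the plan says.** Clusters and study populations (Methods) gives three groups under the words "To be dropped from the analysis will be". The third is "mother-child pairs of children with disability that would make their participation in the intervention difficult", illustrated by "for example, blind, deaf and intellectually impaired individuals or children with cleft lip". It is a rule about the analysis set, not about eligibility.

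Other parts of the article fix when and where it acts:

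- Study design and randomization: "Twelve of the CUs will be randomized with half allocated to the intervention and the other half to the control arm without matching".
- Clusters and study populations, on the women: "These will be recruited during pregnancy on a rolling basis until the desired sample size is achieved".
- Intervention: "The control group will have the usual care only", with routine visits by community health workers. In the intervention arm these workers follow a denser schedule: "After delivery, they will visit the mother weekly in the first month, then once a month until 6 months".
- Discussion, on limitations: "we plan to adopt intention-to-treat analysis", given there as the answer to loss to follow-up. Statistical analysis applies the same principle with the qualifier that it will be used as appropriate.

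**The concern.** A child's disability normally comes to light after the community unit has been allocated and the mother enrolled. Removing the pair at that stage is a post-allocation exclusion, and the test for it refers to an intervention that only one arm receives. For an intervention pair, difficulty in taking part can be seen. For a control pair, someone has to imagine it. The conditions are examples and not a closed list, so discretion remains, and the person exercising it may know the arm.

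If the rule were used more readily in the intervention arm, and the pairs removed were less often exclusively breastfed, the intervention rate would rise without any effect of the programme. A link with feeding is plausible for cleft lip. Intention-to-treat analysis exists to prevent selection of this kind, so the rule and the stated principle pull in different directions.

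**Working it through.** **1. The plan's own sample size (Sample size considerations).** Inputs: 32 % against 50 %, two-sided 5 %, power 80 %, intracluster correlation 0.035, average cluster size 62.5, 10 % loss.

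- Pooled two-proportion formula, mean rate 0.41: n = [1.960 × √(2 × 0.41 × 0.59) + 0.842 × √(0.32 × 0.68 + 0.50 × 0.50)]² / 0.18² = 116.01, rounded up to 117 per arm.
- Design effect: 1 + (62.5 − 1) × 0.035 = 3.1525 (stated as 3.15).
- Total: 2 × 117 × 3.1525 = 737.7, matching the stated 738. Then 738 × 1.10 = 811.8, matching 812, or 406 per arm.

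The figure reproduces, and the point does not depend on it. It supplies the evaluable number per arm: 738 / 2 = 369.

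**2. Worst-case shift in the primary outcome.** The documents give no disability rate, so the share dropped is an assumption: 1 %, 3 % or 5 % of 369, which is 4, 11 or 18 infants (k). Assume also that all drops occur in the intervention arm and that no dropped infant was exclusively breastfed. A true rate p then appears as p × 369 / (369 − k).

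| k | at p = 32 % | shift (points) | at p = 50 % | shift (points) |
|---|---|---|---|---|
| 4 | 32.35 % | 0.35 | 50.55 % | 0.55 |
| 11 | 32.98 % | 0.98 | 51.54 % | 1.54 |
| 18 | 33.64 % | 1.64 | 52.56 % | 2.56 |

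**3. Effect on the false-positive rate.** With 32 % in both arms and design effect 3.15, the standard error of the difference is √(2 × 0.32 × 0.68 / (369 / 3.15)) = 0.061, or 6.1 points. Shifting a two-sided 5 % normal test by the amounts above gives a type I error of 5.04 % (k = 4), 5.30 % (k = 11) and 5.83 % (k = 18). This is an approximation that ignores the small number of clusters.

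**4. Equal application.** If the same k non-exclusively breastfed infants leave each arm and both true rates are 32 %, both observed rates move together and the difference stays at 0. If the true rates are 32 % and 50 %, the 18-point difference becomes 18 × 369 / (369 − k), which is 18.2, 18.6 and 18.9 points. That is a slight change in the population described. It does not create an effect where none exists.

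**The case against.** The strongest objection is to a reading that goes further than the text. A reader might infer that the test means nothing in the control arm, so that pairs can leave the intervention arm only. The article does not support this. The wording is conditional, no arm is named, and the question can be put about any child. The examples are personal characteristics that can be established in either arm.

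A reader might also infer that community health workers, through their more frequent visits, will decide who is dropped. No section gives them that role. Quantitative data collection puts all pairs in both arms on one questionnaire schedule, and study staff measure every child at months 2, 4 and 6, so a cleft lip can be seen equally in either arm. A third inference is that the dropped infants are the ones least likely to be exclusively breastfed. That is plausible for cleft lip but unsupported for blindness or deafness. Some listed conditions are hard to establish by 6 months, which would keep the number of drops low.

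Two further objections have weight. Intention-to-treat is promised with a qualifier and is aimed mainly at loss to follow-up, so the rule is in tension with it and does not flatly contradict it. Who adjudicates, and by what list, may be settled in a full protocol that is not shown.

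These objections limit the size and certainty of the problem but do not remove it. The published rule still takes enrolled pairs out of the analysis after allocation, by a judgement that refers to one arm's treatment.

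**Conclusion.** The point holds as a risk created by the wording. The criterion could be applied unequally, and it fits poorly with intention-to-treat. The documents do not show that it will be applied to one arm.

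The 0.35 to 2.56 points tabulated above are an upper bound that combines three unfavourable assumptions: all drops in one arm, every dropped infant not exclusively breastfed, and up to 5 % dropped. Even so, the bound is small beside the 18-point target and the 6.1-point standard error, and it would be unlikely to change the trial's conclusion. In that scenario the bias favours the intervention. The change is worth making because it is simple and takes a discretionary exclusion out of the primary comparison.

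**What to change.** Remove the third criterion from the analysis drops in Clusters and study populations. Keep these pairs in the primary intention-to-treat analysis, in the arm of their community unit.

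If infants who physically cannot breastfeed are to be set aside, do so only in a sensitivity analysis. Use a closed list of conditions defined without reference to the intervention, have study interviewers record them at the same visits in both arms, and report the counts by arm.

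The cost is a change of wording and a slight dilution of the effect. If the difference is 18 points among the other infants and zero among those retained, the overall difference is 18 × (369 − k) / 369. For k = 4, 11 and 18 this gives 17.8, 17.5 and 17.1 points, a loss of 0.2 to 0.9 points on the same assumed range of 1 to 5 %.

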### Recruitment

Recruitment of the study participants will be done through identification of pregnant women by CHWs, through identification by antenatal care providers in the study area, and through use of community informants to ensure high coverage. All known pregnant women in the two study areas will be invited to participate in the study until the desired sample size is achieved. Recruitment is expected to be for a period of approximately 1 year. Before the beginning of the study, a rigorous community mobilization involving community leaders and community members will be done to inform the community of the study, and to encourage pregnant women to identify with the CHWs as early as possible in both the intervention and control arm. Recruitment will last approximately 1 year from January 2015 to December 2015.

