## Methods

### Study setting

The study will be conducted in Koibatek sub-County, one of the six sub-counties in Baringo County of the North Rift region of Kenya. Residents in Koibatek practise mixed farming in an area that covers 2,306 km^2^. The total population for 2014 (as reported by sub-county Health Registry and Information Office) is 125,637 with 30,203 being women of childbearing age (15–49) and 4,799 of them being children under 1 year. Koibatek sub-county is subdivided into four administrative divisions (Eldama Ravine, Timboroa, Esageri and Torongo). The sub-county is mainly inhabited by the Tugen people, a Nilotic group whose main occupation and economic activity is mixed farming. The sub-county is served by 32 health facilities (26 dispensaries, 5 Health Centers and only 1 sub-county/district hospital) most (close to 90 %) of which are run by the government. The sub-county lies within the Rift Valley region where, according to the 2008/09 Kenya Demographic and Health Survey, the median duration of exclusive breastfeeding, was 1.7 months, which was among the highest in the country, being higher than the national rural average of 1.0 month. Slightly over a third of children are stunted, 20 % are underweight, while only a third of women deliver at a health facility [10]. Other evidence indicates that the prevalence of exclusive breastfeeding for 6 months is 32 % [17].

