### Sample size considerations

The sample size determination was undertaken considering the cluster randomized study design [21]. An estimated sample size of 738 mother-child pairs will be required for both intervention and control arms so as to have adequate power to detect an increase in exclusive breastfeeding for 6 months from 32 % (the baseline rate of exclusive breastfeeding in the study setting) [17] to 50 %; an approximately 18-percentage point increase, although higher increases have been documented in similar interventions elsewhere in the developing world [22]. We used a level of precision of 5 % (for a 2-sided *t* test) and power of 80 %. We then adjusted for expected design effect using a design effect of 3.15 calculated based on intracluster correlation coefficient of 0.035 from another study in Kenya (unpublished) and an average cluster size of 62.5. We allowed for 10 % potential loss to follow-up. The estimated sample size is 812. We therefore expect to recruit 406 women in each study arm. Twelve CUs will be required for the estimated sample size.

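### Women are enrolled after cluster allocation, partly through staff who know the arm, with no target per community unit, so who is enrolled can differ by arm

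*Protocol article*

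**What the plan says.** All places are in the Protocol article.

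- **Recruitment.** Women are found through "identification of pregnant women by CHWs, through identification by antenatal care providers in the study area", and through community informants. The enrolment rule is: "All known pregnant women in the two study areas will be invited to participate in the study until the desired sample size is achieved". Community mobilisation beforehand encourages early contact with CHWs in both arms. Recruitment is to last about a year, January to December 2015.
- **Clusters and study populations.** Recruitment is rolling and aims at the first or second trimester, "so as to get as much exposure to the intervention during pregnancy as possible".
- **Intervention.** CHWs and facility staff in intervention CUs are trained on the package at the start. Counselling begins once a woman is recruited.
- **Trial status.** The intervention has started, and recruitment is expected to close by February 2016.
- **Sample size considerations.** 406 women are expected in each arm. The design effect of 3.15 uses an average cluster size of 62.5 and an intracluster correlation of 0.035. No number is set for each CU.
- **Statistical analysis and Discussion.** Baseline differences will be adjusted for if they appear. Table 5 lists control variables for exclusive breastfeeding, including maternal characteristics and antenatal care.

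**The concern.** Randomising clusters protects the comparison of clusters as they stood at allocation. It does not protect the comparison of women who enter afterwards if the way they enter depends on the arm. Here part of the identification lies with staff who, in one arm, have been trained in the intervention and will deliver it. The reason given for finding women early, more exposure to the intervention, applies only in that arm.

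If the women who become known differ between arms in motivation, antenatal attendance or stage of pregnancy, exclusive breastfeeding may differ for reasons other than the intervention. The outcome is self-reported by mothers and closely tied to motivation, so it is exposed to such selection.

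The second issue is cluster size. With no target per CU, units that identify women quickly can fill more of an arm's 406, and variation in size raises the design effect above the planned value.

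**Working it through.** **1. Order of events.** No single sentence says that allocation precedes enrolment, but three statements imply it. Counselling starts at recruitment, so the arm must already be fixed. Intervention staff are trained at the beginning. The intervention is running while recruitment is open.

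**2. The plan's sample size, reproduced.** Inputs: "We used a level of precision of 5 % (for a 2-sided *t* test) and power of 80" %; an "increase in exclusive breastfeeding for 6 months from 32" % "to 50 %; an approximately 18-percentage point increase".
- Two proportions, pooled variance, no continuity correction: 117 per arm.
- Design effect: 1 + (62.5 − 1) × 0.035 = 3.15.
- 117 × 3.15 = 368.6, rounded up to 369 per arm, 738 in all.
- 738 × 1.10 = 812 after rounding, or 406 per arm.

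Both stated figures reproduce.

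**3. Births available against women needed.** Study setting gives a total population of 125,637, with "4,799 of them being children under 1 year". Clusters and study populations says that CUs "usually have a population size of approximately 5000 people".
- Rate: 4,799 / 125,637 = 3.82 %.
- 12 × 5,000 × 0.0382 = about 2,292 births a year, or about 191 per CU.
- 812 / 2,292 = 35 %, so births are 2.8 times the number needed.
- Average needed per CU: 812 / 12 = 67.7.
- Range over an assumed 4,000 to 6,000 people per CU: 1,833 to 2,750 births, or 2.3 to 3.4 times the need.
- Over 14 months (to February 2016), at 5,000 per CU: 3.3 times.

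Infants under 1 year stand in for pregnancies. Known, consenting women found early enough will be fewer than this. The figure shows only that the target can be met without enrolling every pregnancy, so the arms can differ in which pregnancies are found, and when.

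**4. Cost of unequal CU sizes.** Design effect = 1 + [(1 + CV²) × m − 1] × 0.035, with m = 738 / 12 = 61.5 women analysed per CU. The effective number per arm is 369 / design effect. The CVs are assumed; the article gives none.

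| Size CV | Design effect | Effective n per arm | Power |
|---|---|---|---|
| 0 | 3.12 | 118.4 | 81 % |
| 0.25 | 3.25 | 113.5 | 79 % |
| 0.5 | 3.66 | 100.9 | 74 % |
| 0.75 | 4.33 | 85.3 | 67 % |

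**5. Reach of the safeguards.** Several identification routes help, but antenatal staff in intervention facilities are trained too. Mobilisation covers both arms, but it works by women coming forward to the CHWs. Adjustment reaches measured factors only, and gestational age at enrolment is not named in Statistical analysis or Table 5.

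**The case against.** The other side has a good case, and much of it limits what can be claimed.

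- **A reader might infer that recruitment runs to a pooled total only.** It does not: 406 per arm is stated. Imbalance between CUs within an arm remains possible.
- **A reader might infer that CHWs choose who enters.** The article says that they identify women and that all known pregnant women are invited. It does not say that CHWs select or consent them.
- **A reader might infer that the target fills early and two thirds of pregnancies are shut out.** At full identification, 812 would be reached in 812 / 2,292 × 12 = 4.3 months. The article plans about 12 months, with closure by February 2016. That suggests a flow of known, consenting women not far above 812, so the ceiling may hardly bind. What stands is the narrower point that identification can be more complete, or earlier, in one arm.
- **A reader might infer an inflated effect of some definite size.** Nothing in the document supports a figure, and the direction is open. CHWs who search harder may bring in less motivated women, which would pull the difference towards zero.
- **Early identification is sought in both arms**, and CHWs in both receive a motivation package. This lessens the difference in incentives, but the stated purpose of early recruitment is still exposure to the intervention.
- **An article condenses.** Logs and scripts may stand in the full protocol, and their absence is no fault. The point rests on the enrolment rule and targets that the article does state.

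**Conclusion.** The concern holds in this limited form. Enrolment follows allocation, arm-aware staff take part in identification, and the stated rule sets no number per CU and no listing procedure common to both arms. Differential enrolment is therefore possible, and conditional adjustment for measured factors cannot fully remove it. This rests on the inferred order of events, which the text supports well, and on the births estimate, which depends on about 5,000 people per CU and on the infant proxy.

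The document does not show that bias will occur, how large it would be, or which arm it would favour. The effect on power can be calculated, but only for assumed variation in CU size: minor at a CV of 0.25 (about 79 %), material at 0.5 or above (74 % or less). The change is worth making because it is cheap and acts on both problems.

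**What to change.** In Recruitment:

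1. Set the same target in every CU: 812 / 12, about 68 (12 × 68 = 816). Spread it evenly over the recruitment period, roughly 68 / 12 = 5.7 women a month per CU, so that early-known women do not fill the quota.
2. Build each CU's pregnancy list in the same way in both arms, pooling antenatal registers, informants and CHW reports, with the same gestational-age window.
3. Have the research assistants who already collect baseline data invite listed women, using one neutral script in both arms.

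Because recruitment is under way, apply this to the remaining enrolment. For all women, compare characteristics at enrolment (parity, gestational age) by arm as a check on selection. Any analysis adjusted for gestational age at enrolment should be a sensitivity analysis only, because it is measured after allocation and may itself depend on the arm.

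Cost: a protocol clarification, somewhat slower enrolment in fast CUs, and some added work for existing research assistants. The overall sample size and the intervention stay essentially as planned.
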